## Abstract

**Introduction::**

Postoperative biliary complications in living donor liver transplantation are often difficult to treat, and if treatment is not successful, the patient’s QOL is significantly reduced. The frequency of postoperative biliary complications is reported to be higher than that of deceased donor transplantation. In 2013, Lin et al. reported that while biliary reconstruction has traditionally used a surgical surgical loupe (2.5x–4.5x), biliary reconstruction using a surgical microscope (5x–15x) can reduce the incidence of complications. The objective of this study is to clarify the efficacy of biliary reconstruction using surgical microscope in living donor liver transplantation by a multi-facility, randomized comparative study.

**Methods and analysis::**

It is an open-label randomized controlled study in which target patients who meet the registration requirements are randomly allocated to a surgical loupe group and a microscopy group after obtaining their consent (Ratio 1:1). The primary endpoint is an incidence of biliary complications (bile leakage and anastomotic biliary stricture) with Clavien-Dindo class III or higher within 52 weeks following surgery. The secondary endpoint is length of time required for biliary reconstruction using a surgical microscope.

**Ethics and dissemination::**

This study protocol was approved by the institutional review board of Nagasaki University Hospital (No. 20122102-2). The study is registered in UMIN-CTR as UMIN000042011. Written informed consent will be obtained from all participants. The results will be published in a peer-reviewed journal and will be presented at medical meetings.

**Highlights:**

## Background

Postoperative biliary complications in living donor liver transplantation are often difficult to treat, and if treatment is not successful, the patient’s QOL is significantly reduced, with some cases resulting in cholestatic cirrhosis, which is referred to as the “Achilles’ heel of living donor liver transplantation” [1]. In actual clinical practice, while a surgical loupe (enlargement ratio: 2.5x–4.5x) is used to perform bile duct to bile duct anastomosis, in the case of liver transplantation using a whole liver graft such as brain-dead donor liver transplantation, the diameter of the reconstructed biliary duct may have wider orifice, with the frequency of biliary complications reported to be approximately 10–15% [2,3,4]. On the other hand, in liver transplantation using a partial liver graft such as living donor liver transplantation, the frequency of postoperative biliary complications is reported to be higher than that of deceased donor transplantation approximately at 15–30% because the diameter of the reconstructed biliary duct is small, short and sometimes multiple lumens [5,6,7].

A surgical microscope (5x–15x) is used for hepatic artery anastomosis with a diameter of 2 to 3 mm in living donor liver transplantation; however, not many facilities use them for biliary reconstruction. In 2013, Lin et al. reported a retrospective examination at a single facility that while biliary reconstruction has traditionally used a surgical loupe (2.5x–4.5x), biliary reconstruction using a surgical microscope (5x–15x) can reduce the incidence of complications to the 6% range [8].

## Objective

The objective of this study is to clarify the efficacy of biliary reconstruction using surgical microscopes in living donor liver transplantation, in which good treatment results have been reported, by conducting a multi-facility, randomized comparative study.

## Expected results

If this study proves the usefulness of biliary reconstruction using a microscope, the technique will become one standard technique, with expectations of low incidence of biliary complications following liver transplantation as well as improved patient QOL by performing this technique.

## Study design

It is an open-label randomized controlled study in which target patients who meet the registration requirements are randomly allocated to a surgical loupe group and a microscopy group after obtaining their consent (Ratio 1:1).

The procedures used in this study are as follows: A graft from a living donor is transplanted once the liver of the recipient is completely removed. Revascularization is performed followed by biliary reconstruction. The presence of biliary complications is morphologically evaluated by cholangiography under fluoroscopy or magnetic resonance cholangio-pancreatography (MRCP). In addition, computed tomography and postoperative blood tests (increase in liver enzymes and biliary enzymes) are used for evaluation.

## Endpoints

The primary endpoint is an incidence of biliary complications (bile leakage and anastomotic biliary stricture) with Clavien-Dindo class III or higher within 52 weeks following surgery.

Bile leakage was defined as the presence of bile material in a closed suction drain that persisted more than 7 days after transplantation or as the presence of a biloma around the area of the anastomosis. Anastomotic biliary stricture was defined as an intrahepatic biliary dilatation > 3 mm in the presence of a notable anastomotic narrowing, on the basis of symptoms, or on the basis of abnormal liver function tests. Jaundice, fever, or abdominal pain could be present with a bile leak or stricture. The secondary endpoint is length of time required for biliary reconstruction using a surgical microscope.

## Patient eligibility

Patients scheduled to undergo a living donor liver transplantation at Nagasaki University Hospital, Kyusyu University Hospital and University of the Ryukyus Hospital are targeted.

### Inclusion criteria

Patients meeting all of the following criteria are targeted:

Recipients of living donor liver transplantation that will be performed in the participating facilities of this study from the date the study is approvedPatients who will undergo biliary reconstruction by bile duct to bile duct anastomosisPatients who do not require multiple biliary reconstructions (however, it will not be considered as multiple biliary reconstructions if it forms multiple bile ducts and can be anastomosed as a single hole as a result of bile duct plasty.)Patients who are 18 years of age or olderNo gender restrictionsPatients who voluntarily give their consent to participate in this study upon receiving sufficient explanation and having a good understanding of the details. Patients who are able to provide consent. In addition, regarding patients for whom it is believed difficult to provide effective informed consent, such as when hepatic encephalopathy was caused by hyperammonemia due to the progression of liver failure, consent shall be obtained by their legal representatives. Legal representatives shall include spouses, parents, adult children, adult siblings or grandchildren, grandparents, relatives who share the same household, or individuals believed to be equivalent to those who are closely related.

### Exclusion criteria

Patients who have been deemed ineligible as a study subject by the responsible personnel of the study, such as when choledochojejunostomy is performed or when anastomosis under a microscope is difficult.Patients who did not provide their consent to participate in the study upon receiving sufficient explanation regarding their participation in this study.

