## Registration

The members and principal investigator of each facility shall receive the consent of the subject patient and contact the Department of Surgery, Nagasaki University Graduate School of Biomedical Sciences by fax or e-mail. The Department of Surgery, Nagasaki University Graduate School of Biomedical Sciences will input UMIN INDICE and allocate it. The allocation results (microscopy group or surgical loupe group) will be provided to the participating facility by fax or e-mail so that each site can perform surgery accordingly.

Allocation method: minimizationAllocation factors: type of graft (right liver/left liver), primary disease of the recipient, facility conducting the studyMethod of registering the case: UMIN INDICEInstitution registering the case and conducting the allocation: The Department of Surgery, Nagasaki University Graduate School of Biomedical Sciences

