### Items to collect in the study

Patient background: gender, age, BMI, primary disease, liver function prior to surgery, surgical historyFactors of surgery: Completion rate of biliary reconstruction using a surgical microscope, duration of surgery, length of time required for biliary reconstructionBlood test: hepatic biliary enzymes (AST, ALT, ALP, γGTP), bilirubin (total bilirubin, direct bilirubin) (***Table 1***)Regarding complications: presence of biliary complications: bile leakage (diagnose by drainage and puncture), anastomotic biliary stricture (cases in which treatment such as endoscopic biliary tube insertion or percutaneous cholangiodrainage was required)Cholangiographyn (direct imaging, MRCP): evaluate the presence of anastomotic stricture and the presence of anastomotic leakage (***Table 1***).Abdominal contrast-enhanced CT: evaluate the presence of intrahepatic bile duct dilatation (***Table 1***).

**Table 1 T1:** Items to collect in the study.

ITEM	PRIOR TO SURGERY	FOLLOWING SURGERY	OBSERVATION PERIOD FOLLOWING SURGERY			UPON DISCONTINUATION

Period	0–4 Weeks before	0 weeks	12 weeks following surgery	24 weeks following surgery	52 weeks following surgery	Upon discontinuation

Medical checkup	○	—	○	○	○	○

Obtainment of consent	○	—	—	—	—	—

Random allocation	•	—	—	—	—	—

Patient background	○	—	—	—	—	—

Factors of surgery (total duration of surgery, length of time required for biliary reconstruction)	—	○	—	—	—	—

Blood test (hepatic biliary enzymes, bilirubin)	○	—	○	○	○	○

Regarding complications	—	—	○	○	○	○

Biliary form evaluation (direct imaging or MRCP)	—	—	○			

Abdominal contrast-enhanced CT	○	—	○	○	○	○

To be conducted upon obtaining consent.

Regarding the postoperative observation period, each evaluation date shall be within the acceptable range of ± 28 days.

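### Eligibility can turn on findings at the operation, after an open allocation, so difficult cases could be removed once the arm is known

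*Protocol article*

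**What the plan says.** **Eligibility.** The protocol article's Exclusion criteria give the study's responsible personnel discretion to deem a patient ineligible, "such as when choledochojejunostomy is performed or when anastomosis under a microscope is difficult". These two grounds are examples; no objective threshold and no time point are given. The Inclusion criteria add that patients needing multiple biliary reconstructions do not qualify, except where plasty turns several ducts into one opening.

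**Allocation.** Study design places random allocation after consent. In Table 1 (Items to collect in the study) allocation is marked only in the pre-surgery column, headed "0–4 Weeks before", with a dash at week 0. A footnote that appears to belong to the allocation row reads "To be conducted upon obtaining consent". Under Registration, the result "will be provided to the participating facility by fax or e-mail so that each site can perform surgery accordingly". Study design also states: "It is an open-label randomized controlled study".

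**Surgery.** Study design puts biliary reconstruction after removal of the recipient's liver, implantation of the graft and revascularization. Under Surgical methods, the anastomosis point is chosen in view of the donor duct's diameter and alignment.

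**Data.** The items collected include "Completion rate of biliary reconstruction using a surgical microscope".

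**The concern.** An eligibility rule is harmless to a randomised comparison if it is applied before allocation, or by someone who cannot know the arm. Here neither is required. Whether choledochojejunostomy is performed, and whether plasty gives a single opening, may not be known until the graft is in place. By then the team has known the arm for anything up to four weeks.

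The ground of microscope difficulty adds asymmetry. A surgeon working under the microscope meets the difficulty directly. A surgeon using the loupe would have to judge a technique not in use. The Background links the higher complication rate in living donor transplantation to small, short and sometimes multiple ducts, and the Discussion lists the number and size of ducts among the causes. The cases likely to be called difficult are therefore plausibly the high-risk ones. Removing them from one arm lowers that arm's complication rate without any treatment effect.

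The collected completion rate under the microscope would also look better than it is if patients whose anastomosis was not completed were declared ineligible. The Discussion names versatility as one of the trial's aims, and that rate bears on it.

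**Working it through.** **1. Order of events, set side by side**

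| Step | When | Source |
|---|---|---|
| Consent, then allocation | 0–4 weeks before surgery | Study design; Table 1 |
| Arm sent to the site | Before surgery | Registration |
| Hepatectomy, implantation, revascularization | At surgery | Study design |
| Duct configuration, plasty, choice of anastomosis | At surgery, after the above | Study design; Surgical methods; Inclusion criteria |
| Judgement of ineligibility | No time point given | Exclusion criteria |

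Nothing in the article requires the last step to precede the first.

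**2. The plan's own sample size**

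Inputs from Statistical analysis: 25% against 10%, one-sided 5%, power 80%. The pooled formula without continuity correction, with p̄ = (0.25 + 0.10)/2 = 0.175, is

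n = [1.645·√(2·0.175·0.825) + 0.842·√(0.25·0.75 + 0.10·0.90)]² / 0.15² = (0.884 + 0.443)² / 0.0225 ≈ 78.3, rounded up to 79 per arm, 158 in total.

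This matches the stated figure, with power 80.3%. It leaves no allowance for removal after randomisation.

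**3. What one-sided removal would do**

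Assumptions, none of them from the documents except the 25%: no true effect; 25% risk in both arms; a fraction f of the microscope arm removed, with risk r; nobody removed from the loupe arm.

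Microscope rate after removal = (0.25 − f·r)/(1 − f). Example with f = 0.10, r = 0.50: (0.25 − 0.05)/0.90 = 22.2%.

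The error is the exact binomial probability that the uncorrected one-sided 5% test favours the microscope, with 79 loupe patients against 79(1 − f) microscope patients, rounded.

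| f removed | Microscope n | r | Microscope rate | One-sided error |
|---|---|---|---|---|
| 0 | 79 | – | 25.0% | 5.0% |
| 5% | 75 | 40% | 24.2% | 6.5% |
| 5% | 75 | 50% | 23.7% | 7.6% |
| 10% | 71 | 40% | 23.3% | 8.2% |
| 10% | 71 | 50% | 22.2% | 10.9% |
| 15% | 67 | 40% | 22.4% | 10.4% |
| 15% | 67 | 50% | 20.6% | 15.7% |

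**4. If removal were neutral**

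Removal that is equal in both arms and unrelated to risk causes no bias, only lost power: from 80.3% to 78.5%, 76.5% or 72.1% with 5%, 10% or 20% removed.

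**The case against.** The strongest reply is that removal after allocation is inferred, not stated. The Exclusion criteria are an eligibility list; they do not mention intra-operative findings, withdrawal or exclusion from analysis. The Inclusion criteria are worded prospectively, and the microscope clause can be read as a pre-operative screen for patients unsuited to one of the two techniques, which would be proper. This stands in part: some difficulty could be foreseen. But the choledochojejunostomy ground refers to the procedure as carried out, and no passage confines either ground to the time before allocation.

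Second, the criterion applies to both arms. Choledochojejunostomy and multiple openings are not tied to either technique, and the responsible personnel are not identified as the operating surgeon. This also stands. Unequal removal is a possibility that the wording leaves open; it is not a demonstrated fact.

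Third, the article is a condensed account, and the full protocol or SAP may already keep all randomised patients in their arm. The absence of an analysis-set rule is therefore not the finding. An eligibility rule with no time limit is stated text, and an analysis plan would have to override it.

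Fourth, collecting a completion rate suggests that non-completers may be kept and counted. A reader might infer that the trial cannot answer its versatility question because exclusions push that rate towards 100%. The article does not support so strong a reading.

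Finally, 0–4 weeks is a window that also admits allocation shortly before surgery. That shortens the interval but does not change the order of events.

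**Conclusion.** The point holds as a route to bias in the stated rules. Followed as written, they permit discretionary removal of randomised patients by unmasked personnel, on grounds that can arise at the operation, one of which is met directly only in the microscope arm. Any resulting bias in the primary endpoint from that ground would tend to favour the microscope.

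The size is illustrative: a one-sided 5% error of about 6.5–7.6% with 5% of the microscope arm removed, 8.2–10.9% with 10%, and 10.4–15.7% with 15%. These figures rest on no true effect, 25% risk in both arms, 40–50% risk among those removed, and no removal from the loupe arm. The documents give neither the share removed nor its risk.

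A reader might go further and infer that hard cases will be dropped from the microscope arm, or that the primary analysis is not by allocated arm. The article establishes neither.

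**What to change.** Amend the Exclusion criteria to state that eligibility, including suitability for anastomosis under the microscope, is judged before allocation and without knowledge of the arm, and that it is not a ground for removing a patient already allocated.

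State that the primary analysis keeps every randomised, transplanted patient in the allocated arm. This includes patients converted to the other technique, those who receive choledochojejunostomy and those who need multiple anastomoses. Show an as-treated analysis as a sensitivity analysis. If the full protocol or SAP already says this, align the eligibility text with it.

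Count microscope anastomoses that were not completed in the denominator of the completion rate.

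Optionally, release the allocation in the operating room once a single duct-to-duct anastomosis is confirmed and before it begins. That would settle most of these facts before the arm is known.

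The cost is a short amendment and slight dilution of the treatment contrast from conversions kept in their arm. The optional step adds the logistics of obtaining an allocation during surgery.

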## Registration

The members and principal investigator of each facility shall receive the consent of the subject patient and contact the Department of Surgery, Nagasaki University Graduate School of Biomedical Sciences by fax or e-mail. The Department of Surgery, Nagasaki University Graduate School of Biomedical Sciences will input UMIN INDICE and allocate it. The allocation results (microscopy group or surgical loupe group) will be provided to the participating facility by fax or e-mail so that each site can perform surgery accordingly.

Allocation method: minimizationAllocation factors: type of graft (right liver/left liver), primary disease of the recipient, facility conducting the studyMethod of registering the case: UMIN INDICEInstitution registering the case and conducting the allocation: The Department of Surgery, Nagasaki University Graduate School of Biomedical Sciences

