## Discussion

Biliary complication is more frequent in living donor liver transplantation than deceased donor liver transplantation [5,6,7]. Biliary complication is associated with outcomes of liver transplantation in terms of graft function and quality of life. For anastomotic stricture, an endoscopic approach and percutaneous transhepatic cholangiodrainage (PTCD) are required after surgery, and hepaticojejunostomy may be performed in some cases [9]. Endoscopic management of biliary stricture is technically more challenging in LDLT than in DDLT, because of the complexity of the biliary anastomosis including multiple anastomosis, tortuous and angulated biliary anatomy. Even after the successful endoscopic approach, multiple stent exchange to prevent stent occlusion is needed. In also patients with PTCD, multiple exchange of drainage tube is usually needed. Since quality of life is often disturbed in patients with biliary stricture despite the development of postoperative intervention, prevention of biliary complication is highly important.

For preventing biliary complications, various ideas have been implemented from a surgical point of view. For example, the ischemia to the bile duct stumps, the number and size of bile ducts has been reported as causes of biliary complication. The efficacy of minimal hilar dissection to preserve maximal vascular integrity of the bile duct in recipient surgery [5]. With respect to the number of bile ducts in the graft, we have been performing intraoperative cholangiography with radiopaque filament encircling bile duct to detect the appropriate cut point [10].

As one of the important innovations, biliary reconstruction with a microsurgical technique [11]. This approach has the technical advantage of enhanced visualization of the operative field including biliary reconstruction for conspicuously small bile duct [11]. The technique is considered effective to prevent physical trauma to the bile duct epithelium and conduct more precise placement of stitches during the biliary anastomosis.

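### The arm reaches the site before the operation, so earlier steps that bear on biliary complications, and operative eligibility, can be handled with the arm known: a possible, avoidable bias

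*Protocol article*

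**What the plan says.** All references are to the protocol article.

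- **Blinding (Study design).** "It is an open-label randomized controlled study in which target patients who meet the registration requirements are randomly allocated" to loupe or microscope, 1:1.
- **Timing (Items to collect in the study, Table 1).** The row "Random allocation" is marked only in the pre-surgery column, 0–4 weeks before. The note under the table, "To be conducted upon obtaining consent", appears to belong to that row, which carries its own symbol.
- **Disclosure (Registration).** The coordinating department enters the case, and the result "will be provided to the participating facility by fax or e-mail so that each site can perform surgery accordingly".
- **Order of steps (Study design).** The recipient liver is removed and the graft implanted. Then: "Revascularization is performed followed by biliary reconstruction".
- **What differs (Surgical methods).** The two descriptions match on choice of anastomosis point, suture, knots and tube. Only the magnification differs, 5x–15x against 2.5x–4.5x.
- **Risk factors (Discussion).** The article states that "the ischemia to the bile duct stumps, the number and size of bile ducts has been reported as causes of biliary complication". Among preventive surgical measures it lists "The efficacy of minimal hilar dissection to preserve maximal vascular integrity of the bile duct in recipient surgery", and on the number of graft ducts it adds that "we have been performing intraoperative cholangiography with radiopaque filament encircling bile duct to detect the appropriate cut point".
- **Eligibility (Inclusion and Exclusion criteria).** Entry requires a single anastomosis, if necessary after plasty. Exclusion covers choledochojejunostomy and cases where a microscopic anastomosis would be difficult.

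**The concern.** Randomisation balances what exists before allocation. It does not balance what a team does afterwards with the arm known. Here the part of the operation that differs by arm comes late, and the arm is released before all of it. Between release and reconstruction lie discretionary steps that the article itself connects with the primary endpoint.

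If more care were taken over the hilum or the cut point in one arm, or if operative findings were judged differently by arm, the chi-square comparison would credit or debit that difference to magnification. Either direction is conceivable. The analysis could not reliably separate the two afterwards, because the earlier difference would travel with the arm. The minimisation factors (graft type, primary disease, facility) do not cover these steps. Masked outcome assessment would not help either, since the difference would lie in the patients and not in how they are assessed.

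**Working it through.** **1. Is the arm known before steps that matter?**

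| Step | Before or after release of the arm | Differs by design? | Connected in the article with biliary complications or eligibility? |
|---|---|---|---|
| Donor duct division | after | no | yes: number of ducts, cut point |
| Recipient hilar dissection | after | no | yes: stump ischemia, hilar dissection |
| Any bile duct plasty, single-hole judgement | after | no | yes: number of ducts, inclusion criterion |
| Judgement that microscopic anastomosis is difficult | can be after | no | yes: exclusion criterion |
| Choice of anastomosis point, suturing | after | inside the allocated procedure | yes: the intervention itself |

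The first four rows need no knowledge of the arm. The last row does.

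**2. The plan's own sample size.** Inputs from Statistical analysis: 25% against 10%, one-sided 5%, 80% power.

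n per group = [z(0.95)·√(2p̄(1−p̄)) + z(0.80)·√(p1(1−p1)+p2(1−p2))]² / (p1−p2)², with p̄ = 0.175

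= [1.645·√(2×0.175×0.825) + 0.842·√(0.1875+0.09)]² / 0.15²

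= (0.884 + 0.443)² / 0.0225 = 78.3, rounded up to 79, so 158 in total. The stated figure is reproduced. Moving the release of the arm does not change it.

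**3. Illustration: no true microscope effect, better earlier steps in the microscopy arm.** The article gives no size for such a shift, so odds ratios (OR) of 0.9, 0.8 and 0.7 are assumed, acting in one direction on the whole arm. The base odds are 0.25/0.75 = 0.333. Rate = 0.333·OR / (1 + 0.333·OR), for example 0.30/1.30 = 23.1%.

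The chance of a significant result favouring the microscope is the sum of the binomial probabilities, 79 per group, over all outcomes where the uncorrected pooled z exceeds 1.645 (one-sided 5%) or 1.960 (two-sided 5%).

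| Assumed OR | Loupe | Microscopy | One-sided | Two-sided |
|---|---|---|---|---|
| 1.0 | 25% | 25.0% | 5.0% | 2.6% |
| 0.9 | 25% | 23.1% | 8.7% | 4.8% |
| 0.8 | 25% | 21.1% | 14.7% | 8.6% |
| 0.7 | 25% | 18.9% | 23.7% | 15.2% |

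Both columns are needed. The one-sided 5% is stated for the sample size, while for the final test the article says only that the significance level is 5%. As a cross-check, the normal approximation for a 2-point fall gives 8.8% one-sided and 4.8% two-sided, in line with the OR 0.9 row (1.9 points).

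**4. The other direction: true 25% against 10%, better earlier steps in the loupe arm.** With the loupe rate lowered to 23.1%, 21.1% and 18.9% against 10%, the same enumeration takes one-sided power from 81.3% to 72.6%, 61.4% and 48.0%.

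**The case against.** The case on the other side has several parts.

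- **The trial is openly unblinded, and allocation before surgery is stated consistently.** This stands: nothing is contradictory. The point concerns a design choice. Operators cannot be masked at the anastomosis, but they can be during the steps before it.
- **The mechanism is inferred.** This stands. A reader might infer that teams will dissect or cut differently by arm. The article says no such thing. It describes cholangiography for the cut point as an existing routine of the authors, admits only single anastomoses, and states that all sites are experienced. The full protocol may also standardise these steps.
- **Some knowledge of the arm is needed.** This stands in part. A reader might infer that everything before suturing could be done without knowing the arm. The article, however, places the choice of recipient anastomosis point inside the procedure described for each arm. Preparing ducts to suit the technique could also be seen as part of a pragmatic comparison of strategies, although the stated objective is the efficacy of reconstruction with a microscope.
- **The percentages have no documentary basis.** This stands. A reader might take them as the expected bias. They rest on assumed odds ratios and a uniform shift across three sites, and the one-sided column also assumes a one-sided final test.
- **In-theatre release is not free.** This stands. Allocation now runs by fax or e-mail through one department.

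What survives is that the early disclosure is written into the article, is not needed for the earlier steps, and leaves open a route to bias that could be closed.

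**Conclusion.** The point holds as an avoidable exposure, not as a demonstrated bias. The article schedules allocation before surgery and sends the result to the site for use in the operation. It names the facility, not the surgeons, as recipient, but in an open-label trial whose sites are to operate accordingly, the plain reading is that the team can know the arm. It can then know it during steps that the article connects with biliary complications, and while operative eligibility is judged. The eligibility route rests most directly on the text, because the criteria depend partly on operative findings.

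Size and direction are unknown. The illustration in the working shows only that, with 79 per group, modest systematic differences in the earlier steps would matter on either reading of the final test. It does not show that the trial's result will be wrong. The change is worth making as a cheap improvement.

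**What to change.** Keep consent, registration and entry of the minimisation factors before surgery; all three factors can be entered then. Release the arm to the operating team only after donor duct division, recipient hilar dissection, revascularization and confirmation of operative eligibility (including any plasty needed to reach a single anastomosis), and immediately before the allocated procedure in Surgical methods begins, including the choice of anastomosis point.

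Two places change:

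- **Registration:** replace the sentence on sending the result to the facility with release in theatre at that point.
- **Table 1:** move random allocation, or at least its disclosure, from the pre-surgery column to week 0, and align the note below the table.

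The cost is a protocol amendment and some logistics. The fax or e-mail route must give way to one that can be reached during every operation at three hospitals, with a fallback if it fails. The microscope must also be available for the biliary step in every case. The Background says that one is used for hepatic artery anastomosis in living donor transplantation, which helps but does not guarantee availability for the later step. The sample size stays at 158, and no procedure or assessment is added for patients.
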